### Inclusion Criteria

• The index child will be rated by their teacher as borderline for concern or above on the screening measure - Teacher Strengths & Difficulties Questionnaire [24]

• The child will be 4-8 years of age

• The child and parent speak fluent Welsh and/or English

• The parent understands the information given and consents to:

◦ Their child attending the programme

◦ Their child being observed

◦ Their child completing a problem-solving task and being audio-recorded

◦ Completing questionnaires about themselves and their child

◦ Their child being randomly allocated

◦ The programme delivery being filmed for facilitators' supervisory meetings and to establish level of fidelity in delivery

◦ Their child's school academic and attendance records being accessed

### Exclusion criteria

Other than the negative of the inclusion criteria no additional exclusion criteria are imposed.

### Intervention

The IY Therapeutic Dinosaur Programme [22] is an 18-week (2 hours/week) child-training curriculum that strengthens children's social, emotional, behavioural & academic competencies. It is delivered to groups of up to six children.

It is part of the successful evidenced based IY Series, a suite of programmes which include parent, child and teacher programmes. All IY programmes are manualised and require trained facilitators.

The programme will be delivered during school time as part of the typical school day. School staff will receive training prior to programme delivery, and will receive supervision throughout delivery to ensure that the programme is delivered as it was developed.

The programme promotes understanding & communicating of feelings, problem-solving strategies, managing anger & friendships. Puppets, role-play, and video clips are used to make it a fun learning experience.

The Dinosaur School programme sessions cover six separate programmes:

1. Making new friends and learning school rules;

2. Dina Dinosaur teaches how to do your best in school;

3. Understanding and detecting feelings;

4. Detective Wally teaches problem-solving steps (including anger management);

5. Molly Manners teaches how to be friendly;

6. Molly explains how to talk to friends.

Wally, Molly and Dina Dinosaur are puppets. Children relate better to puppets than to therapists and are more likely to imitate their appropriate behaviour [23]. Each session includes activities such as "feelings" and "let's suppose" games, co-operative art projects and guessing games to improve co-operation skills. Group leaders praise and reward appropriate behaviours by labelling the behaviour and awarding "dinosaur chips". Weekly homework activities involve the child talking to their parent/s about what they have learned to encourage positive parent-child interaction.

For more programme information see http://www.incredibleyears.com

### Facilitators

The IY Teacher Classroom Management training and the IY Classroom Dina curriculum training has been undertaken by staff in all of the proposed schools. All facilitators will undergo the additional IY Therapeutic Dina training prior to delivery. The 40 facilitators will be teachers and/or classroom assistants working in the participating schools.

During intervention delivery facilitators will attend supervision meetings led by an IY trainer (the second author) once per month during the 18 weeks, for delivery support and to ensure implementation fidelity. Clips from their taped sessions will be played to facilitate discussion and feedback.

School-based delivery support will be provided by a teacher seconded to IY Cymru for the duration of the intervention delivery.

### Measures

Measures will be completed by teachers, parents, children and facilitators and collected by the research team. Demographic questionnaires will be completed by parents and teachers at baseline only. Primary and secondary measures will be administered at all time points.

*The primary outcome measure *is the Teacher SDQ, also used here as the screening measure. It is a 25-item inventory to assess the occurrence of particular behaviours that have been associated with conduct problems, hyperactivity, emotional symptoms, peer problems and pro-social behaviour in children aged 4-16. A high total difficulties score denotes higher occurrence of problematic behaviours [24].

#### Secondary outcome measures

For children:

• The Eyberg Child Behaviour Inventory across all time points is a 36-item inventory, completed by the parent for the assessment of frequency and intensity of behavioural problems in children aged 2-16 years [25]. A high score in each of the subscales denotes more frequent/intense problem behaviour.

• The Bangor Dinosaur School Questionnaire has been developed by [name] [26], to assess levels of social and emotional competence. A high score denotes higher rates of social/emotional competence.

• The Wally Problem Solving test assesses children's problem-solving skills and solution types (positive and negative) in response to hypothetical problem situations http://www.incredibleyears.com.

• Blind observation of peer interaction to assess friendship skills (observation tool under development)

• Child interview to ascertain number of friends a child has

• Academic attainment - assessed by school records

• School attendance - assessed by school records

For parents (self-reports):

• The Parenting Scale questionnaire [27] is a 30-item inventory is designed to measure dysfunctional discipline practices in parents of children aged 1.5 to 4 years, but has been used successfully in older children up to age sixteen [8]. A high score denotes high rates of dysfunctional practices.

• The Beck Depression Inventory [28] is a 21-item measure to assess the severity of characteristic attitudes and symptoms associated with depression. A high score relates to increased levels of depression.

• The Warwick-Edinburgh Mental Well-being Scale (WEMWBS) [29] is a 14-item positively worded measure assessing mental health. The higher the score the higher the levels of well-being.

For teachers (self-report):

• The Teacher Stress Inventory (TSI) [30] is a 20-item measure to examine the effect of difficult classes, impolite pupils and maintaining class discipline on teacher stress levels. The higher the score the higher the stress levels.

Additional measures relating to programme delivery and child responsiveness consist of:

• Implementation fidelity checks - facilitator-completed after each week's session has been delivered

• Child Dina homework completion rates - facilitator assessed

• Attendance levels of child at Dina group - facilitator assessed

### Data Collection

Parent measures will be completed during home visits by the research team. A £10 cash incentive will be paid to the parent at the end of each data collection visit on completion of measures.

Teacher measures will be completed independently during school time and collected by researchers.

Child data will be collected by researchers during school time, by prior arrangement with the schools.

Research staff will be trained in the observational tool until 70% inter-rater reliability is obtained. At least 20% of 'blind' observations will occur with two researchers to gauge inter-rater reliability. Frequent practice and trouble-shooting meetings will be held to maintain reliability levels.

Facilitator implementation checklists and child programme attendance will be collected after each weekly Dina session.

Teacher and child attendance levels will be collected for each term. Child academic attainment, by means of expected and achieved grades, will be collected at each time point from Gwynedd Education Central database, or requested through individual schools.

### Sample size and power calculation

The programme will be delivered to a maximum of six children within a group format. To account for any potential difficulties in recruitment or attrition the power calculation was conducted based on 4 children per condition per school, i.e. N = 160, 33% below the agreed target of 240.

A factorial design with two factors of condition and school with two and twenty levels has forty cells (treatment combinations). A total of 160 participants are required to provide 4 participants per cell. This design achieves 88% power at a 5% significance level.

### Randomisation

This is a pragmatic, parallel, RCT, with children individually randomised on a 1:1 basis, intervention or waiting-list control.

Individual (child) block randomisation within school will be applied with gender as the stratification variable. The North Wales Organisation for Randomised Trials (NWORTH), an independent registered trials unit, will perform the randomisation process using a computer programme written specifically for this trial. Randomisation will occur after eligibility has been established, informed consent obtained and baseline measures collected from parents.

### Blinding

Randomisation will be conducted by NWORTH, with results of allocation forwarded to the Principal Investigator; all other researchers will be blind to condition. Parents, children and teachers will not be blind. Participants (parents and children) will be respectfully asked not to discuss the intervention with the researchers during follow-up interviews and collection of the research measures.

### Statistical analyses

Characteristics of the sample (child and parent) will be analysed and differences (if any) between the two conditions, intervention and control (and lost participants), will be recorded.

Demographic variables (e.g. parental status, ethnicity, education and income levels) will inform the mediator and moderator analysis - for whom the intervention worked best and why.

The main analysis is intention to treat (ITT), to include all participants regardless of protocol deviations and participant compliance or withdrawal, performed according to the assigned treatment group.

In addition to the ITT analysis a per protocol analysis will be conducted on data from participants who have remained in the study, attended at least one intervention session and have completed measures at each time point.

Different methods of dealing with missing data will be explored following data collection and establishment of how many and what type of missing values are achieved.

The difference between the intervention and control conditions on follow-up scores will be based on a mixed model analysis of covariance (ANCOVA), run on SPSS, of the response taking account of the random school effect, fixed treatment effect, gender, age/school year, and the baseline response value. Any similarities within the intervention group, due to participating in a group format intervention, will be controlled for in the model.

Effect sizes will be calculated using Cohen's (1988)[31] guidelines.

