**Methods/Design:**

This is a pragmatic, parallel, randomised controlled trial.

Two hundred and forty children (aged 4-8 years) rated by their teacher as above the 'borderline cut-off' for concern on the Strengths and Difficulties Questionnaire, and their parents, will be recruited.

Randomisation is by individual within blocks (schools); 1:1 ratio, intervention to waiting list control.

Twenty schools will participate in two phases. Two teachers per school will deliver the programme to six intervention children for 2-hours/week for 18 weeks between baseline and first follow-up. The control children will receive the intervention after first follow up.

Phase 1 comprises three data collection points - baseline and two follow-ups eight months apart. Phase 2 includes baseline and first follow-up.

The Therapeutic Programme includes elements on; Learning school rules; understanding, identifying, and articulating feelings; problem solving; anger management; how to be friendly; how to do your best in school.

Primary outcomes are; change in child social, emotional and behavioural difficulties. Secondary outcomes are; teacher and parent mental wellbeing, child academic attainment, child and teacher school attendance. Intervention delivery will be assessed for fidelity.

Intention to treat analyses will be conducted. ANCOVA, effect sizes, mediator and moderator analyses will be applied to establish differences between conditions, and for whom the intervention works best for and why.

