#### Secondary questions include

1. For which children is the intervention most effective?

2. What are the environmental/contextual circumstances that improve the likelihood of success?

3. Does behaviour change in school generalise to the home?

4. Does the duration of time participating in an intervention affect the likelihood of success, that is, is there a dosage affect?

5. Can the intervention be implemented efficiently and effectively with fidelity by teachers in mainstream schools?

6. Does the mental health of teachers and parents of the intervention children improve?

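### The per-protocol rule is not written by arm or by time point: as worded it leaves no controls at first follow-up and drops Phase 1 children for missing a later visit

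*Protocol article*

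**What the plan says.** The protocol article, Statistical analyses, puts intention to treat first: "The main analysis is intention to treat (ITT), to include all participants regardless of protocol deviations". It then adds that "a per protocol analysis will be conducted on data from participants who have remained in the study", with two further conditions: that they "attended at least one intervention session and have completed measures at each time point". Neither condition is limited to one arm or tied to a particular follow-up.

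Four other statements bear on the rule:

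- **Control exposure.** The abstract (Methods/Design) says "The control children will receive the intervention after first follow up". Method and design places this in the following school year and makes it conditional on the programme being effective.
- **Waves.** Method and design gives Phase 1 a baseline and two follow-ups eight months apart, and Phase 2 a baseline and first follow-up only.
- **Length of programme.** Under Intervention, the programme is "an 18-week (2 hours/week) child-training curriculum".
- **Attendance data.** Under Data Collection: "Facilitator implementation checklists and child programme attendance will be collected after each weekly Dina session".

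**The concern.** A per-protocol set has to contain both arms if it is to compare them. A condition that one arm cannot meet before the outcome is measured removes that arm. A completeness condition that reaches beyond the outcome being analysed removes children whose data for that outcome are complete, and here it does so in one phase only.

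The article does not leave this definition to a later document. It states a rule, and an analyst who programmed that rule would get the wrong set. At stake is whether the supplementary comparison can be run at all as written and, if the session clause is repaired informally, whether Phase 1 children are lost from it without need.

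**Working it through.** The plan gives no figure for the size of the per-protocol set, so there is none to reproduce. The check applies the rule to the stated design.

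**Inputs** (Participants; Method and design; Intervention): 20 schools, 10 per phase, 12 children each, 6 per arm. That gives 20 × 12 = 240 children, 120 per arm, and 10 × 12 = 120 children (60 per arm) in each phase. There are 18 weekly sessions of 2 hours, or 36 hours.

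**Step 1: session condition, control arm, literal reading.**

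| Follow-up | Controls who can have attended a session by then |
|---|---|
| First, Phase 1 | 0 of 60 |
| First, Phase 2 | 0 of 60 |
| Second, Phase 1 | up to 60, if the programme is delivered to them |
| Second, Phase 2 | no such wave; any sessions come after their last measurement |

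At first follow-up the literal set has 0 + 0 = 0 of 120 controls. The controls who could enter by second follow-up do so through attendance that comes after the first follow-up outcome. Using them in the first follow-up comparison would select on a later event.

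**Step 2: completeness condition.** This step sets the session condition aside, so it also applies under the intervention-arm-only reading. The article gives no loss rate. Assume a proportion L of children is lost at each follow-up, independently of earlier waves. Phase 2 then keeps 1 − L. Phase 1 keeps (1 − L)², although 1 − L have the data that the first follow-up comparison needs. The share dropped without need is (1 − L) × L.

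| Assumed L | Phase 2 kept | Phase 1 kept | Phase 1 dropped despite complete first follow-up data |
|---|---|---|---|
| 5% | 95% | 0.95² = 90.25% | 0.95 × 0.05 = 4.75%, about 6 of 120 |
| 10% | 90% | 0.90² = 81% | 0.90 × 0.10 = 9%, about 11 of 120 |
| 20% | 80% | 0.80² = 64% | 0.80 × 0.20 = 16%, about 19 of 120 |

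The direction follows from the rule itself. The sizes are illustrations over assumed rates.

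**Step 3: what the session condition does in the intervention arm.** The minimum exposure is 1/18 = 5.6% of sessions, or 2 of 36 hours. The condition removes only children with no attendance at all. As an illustration, assume a child attends each session independently with probability p, so that P(at least one) = 1 − (1 − p)^18.

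- p = 0.10: 1 − 0.90^18 = 0.85
- p = 0.30: 1 − 0.70^18 = 0.998

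Even a child who rarely attends will nearly always qualify. On attendance, the set will therefore be close to the intention-to-treat set.

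**The case against.** The strongest reply is that Step 1 is too literal. The same section describes the analysis as a difference between intervention and control conditions, so a per-protocol analysis without controls cannot have been meant. The session clause was evidently intended for children who were offered sessions. That is a fair account of the intent, and one added clause repairs the wording. It does not rescue the completeness clause, which is faulty under either reading.

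A reader might go further than the text allows in four ways:

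- **That the rule excludes every control child throughout the study.** It does not. Phase 1 controls may attend sessions before second follow-up. The count of zero holds at first follow-up, on the literal wording.
- **That the trial's main conclusion is at risk.** The per-protocol set is an addition to intention to treat in a trial described as pragmatic.
- **That one session is the wrong threshold.** It is lenient, but it was fixed in advance, and the documents give no basis for another number.
- **That the dosage question, "Does the duration of time participating in an intervention affect the likelihood of success, that is, is there a dosage affect", is left to confounded comparisons.** The article does not say how it will be modelled. That may sit in an analysis plan not shown here, and attendance, homework completion and fidelity are measured separately. The article's silence supports no finding.

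One further caution stands. Once the session condition applies to one arm only, the comparison is no longer strictly randomised, and any stricter minimum would select more strongly. This is a reason to label the analysis as supportive.

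**Conclusion.** The rule is wrong as written, in a supplementary analysis, and should be fixed.

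Two faults stand. First, the literal per-protocol set has no control arm at first follow-up (0 of 120 planned). This rests on controls receiving no session before that point, as the article states. Second, tying completeness to every wave treats the phases differently and drops Phase 1 children who have the data for the first follow-up comparison. This rests only on the stated numbers of waves. How many children are lost is unknown: about 6 to 19 of 120 if 5% to 20% are lost per wave, assuming independent losses.

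The one-session minimum is not an error. It does limit interpretation: agreement between this set and intention to treat would say little about adequate delivery.

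**What to change.** Restate the per-protocol set in three parts:

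1. **Session condition:** intervention arm only, at least one session attended before the follow-up being analysed. No session condition for controls.
2. **Completeness:** baseline and the follow-up being analysed, in both arms and both phases. For the main comparison this means baseline and first follow-up. Missing the second follow-up should affect only analyses of that wave, which exists in Phase 1 only.
3. **Reporting:** describe the set as supportive and close to intention to treat, and note that attendance selects in one arm only. If the trial team wants a stricter minimum, it should fix and justify one before outcome data are examined. Because the principal investigator receives the allocations, unblinding is not a usable cut-off.

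A complier-average causal effect analysis is optional. If added, it should state that it assumes allocation affects the outcome only through attendance, which is doubtful when unblinded teachers rate the primary outcome. If sessions attended are the exposure, it should also state the assumption of a linear effect per session. Its interval would be wider.

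The required change costs a few sentences. Attendance is already collected weekly, no new data are needed, and the main analysis and sample size are untouched.

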### Participants

Twenty schools will be identified and recruited in conjunction with Gwynedd Education Services.

In total 240 children will participate (120 intervention, 120 control) across the 20 schools. The 240 children, aged 4-8 years will be identified as scoring at least borderline for concern on the total difficulties score of the Teacher Strengths and Difficulties Questionnaire [24].

The primary caretaker or parent (n = 240) will complete measures on themselves and their child.

Teachers with a participating child in their class will complete a brief demographic form and a measure of teacher stress; Teacher sample size will be determined after recruitment of families.

Forty facilitators (teachers, or teachers partnered with classroom assistants), two from each school, will deliver the intervention to the children. The facilitators will be chosen by the school and will have undertaken relevant IY training to enable delivery.

Participant summary:

• 20 schools (10 in each phase)

• 240 children, 12 in each school, 6 intervention and 6 waiting list control

• 240 parents (primary caretaker of child participants)

• Teachers (of participant children, n = TBC following recruitment of families)

• 40 facilitators (teachers and classroom assistants)

See Additional File 2 for the Consort diagram of flow of participants.

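### The primary model has no term for the teacher who rates the primary outcome; adding one is a cheap gain in precision, probably small and of unknown size

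*Protocol article*

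**What the plan says.** Under Measures, the primary outcome "is the Teacher SDQ, also used here as the screening measure". Under Participants, the target is "240 children, 12 in each school, 6 intervention and 6 waiting list control". The same section says "Teachers with a participating child in their class will complete a brief demographic form and a measure of teacher stress", and leaves the number of teachers open until families have been recruited.

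Under Randomisation, the child is the unit: "Individual (child) block randomisation within school will be applied with gender as the stratification variable". Class and teacher are not strata.

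Under Statistical analyses, follow-up scores are compared by a mixed-model ANCOVA "taking account of the random school effect, fixed treatment effect, gender, age/school year, and the baseline response value". A second sentence adds: "Any similarities within the intervention group, due to participating in a group format intervention, will be controlled for in the model". These are the only clustering terms named. The protocol does not say whether the same teacher rates a child at baseline and at follow-up, eight months apart.

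**The concern.** Two children rated by the same teacher share that teacher's strictness and the same classroom. With twelve trial children aged 4 to 8 in a school, it is a fair inference, though not a stated fact, that many teachers will rate more than one of them and that some will rate children in both arms.

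The listed terms cover this only in part:

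- The random school effect takes up the part of severity that raters in a school have in common, not the differences between them.
- Age or school year is a covariate common to all schools, so it cannot represent one strict teacher in one school.
- The intervention-group term concerns the treated arm only.
- The baseline Teacher SDQ removes stable severity in part if the same teacher rates both times, and less if the rater changes.

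What remains is within-school difference between raters. Allocation is not balanced by class, so a chance excess of one arm under a strict rater adds noise to the treatment contrast. A teacher term would remove some of that noise by giving weight to comparisons within teacher. What is at stake is the width of the confidence interval, in a trial whose power calculation allows for as few as 160 children.

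**Working it through.** **The plan's own figure.** "A total of 160 participants are required to provide 4 participants per cell": 2 × 20 × 4 = 160, which is 1 − 160/240 = 33% below target. Both check. The stated 88% power cannot be reproduced from the protocol's inputs, because no effect size or SD is given. Back-solving with 80 per arm and a two-sided 5% test (sidedness assumed), a standardised difference of 0.5 gives Φ(0.5/√(2/80) − 1.96) = Φ(3.162 − 1.960) = 88.5%, or 88.0% from a noncentral t with 160 − 40 = 120 error df. So d ≈ 0.50 is implied, but it is not a figure from the protocol. The 88% does not depend on a teacher term.

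**Inputs for the check.** From the protocol: 20 schools (S), n = 12 children per school, 6:6 randomised within school. Assumed: variances as shares of a total of 1, with school 0.05, rater ρ = 0.05 to 0.3 (what is left after baseline adjustment) and child residual 0.95 − ρ; in addition, a variance γ = 0.05 shared by the intervention children of a school; and m children per rater.

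**Without the teacher term.** The variance of the treatment effect, averaged over allocations, is

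Var₀ = [4/(S·n)] × [(0.95 − ρ) + ρ(n − m)/(n − 1)] + γ/S.

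Example with m = 4 (three raters) and ρ = 0.2: [4/240] × [0.75 + 0.2 × 8/11] + 0.05/20 = 0.01492 + 0.00250 = 0.01742. Averaging over 200 random sets of allocations gave 0.01746.

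**With the teacher term.** Generalised least squares with the full covariance, averaged over the same allocations, gave 0.01634. The ratio is 0.01746/0.01634 = 1.069.

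**Extra variance without the teacher term, 12 per school, γ = 0.05:**

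| Raters per school (children each) | ρ = 0.05 | ρ = 0.1 | ρ = 0.2 | ρ = 0.3 |
|---|---|---|---|---|
| 1 (12) | 0% | 0% | 0% | 0% |
| 2 (6) | 0.6% | 2.1% | 6.7% | 13.8% |
| 3 (4) | 0.5% | 1.8% | 6.9% | 15.1% |
| 4 (3) | 0.4% | 1.5% | 5.9% | 13.1% |
| 6 (2) | 0.2% | 0.9% | 3.8% | 9.0% |
| 12 (1) | 0% | 0% | 0% | 0% |

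The zero rows follow from the structure. With one rater per school the rater effect is the school effect; with one child per rater it cannot be separated from the child residual.

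**Validity.** The variance that the model without the term would report agreed with its true variance to within about 1% in every cell.

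**Sensitivity.** For 2 to 6 raters at ρ = 0.1, 0.2 and 0.3, leaving out the planned group term (γ = 0) gives about 1-2%, 5-8% and 11-18%. With γ = 0.10 it gives about 1-2%, 3-6% and 8-12%.

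**Power.** At 160 children with 4 per rater, d = 0.5, a school variance of 0.1 against a non-school variance of 1, and no group term, the teacher term moves power from 89.2% to 89.3% (ρ = 0.05), 89.8% to 90.3% (0.1), 91.1% to 92.6% (0.2) and 92.6% to 95.1% (0.3). Here ρ is the rater share of the non-school variance.

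**The case against.** The strongest reply is that nothing here is wrong. Randomisation within school together with a random school effect gives a valid test, and a valid model that could be somewhat sharper is a matter of preference. That stands as to severity: this is an optional improvement, not an error.

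A second reply is that a journal article may leave the full random-effects structure to an analysis plan. That is arguable. But the section does list its model terms and deals with clustering at two levels, so adding the rater is a change to a stated model rather than a request for missing detail.

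A third reply is that every driver of the size is assumed. That is correct. It is also correct that the comparison treats the variance components as known. With few children per teacher and two other random terms, they may be poorly estimated, so the realised gain could be smaller than the table shows.

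A reader might go further and infer that ignoring the rater biases the estimate, understates its standard error or undermines the 88% power figure. The documents do not support this: children are randomised individually within school, the check shows a valid standard error, and the power figure makes no use of a teacher term. Nor does all rater severity fall into the residual, since the school effect and the baseline score take up part of it. A loss as high as 18% arises only if the intervention-group term that the protocol plans is left out of the calculation.

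**Conclusion.** The point holds as a minor, low-cost improvement. The primary model omits the source of correlation closest to how the primary outcome is measured, and the only consequence is some lost precision.

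Under the assumptions used, the loss in variance runs from 0% to about 15%. Since √1.15 = 1.07, the standard error is at most about 7% larger than it need be. In whole schools, 20 − 20/1.01 = 0.2 at about 1% and 20 − 20/1.15 = 2.6 of the 20 at the top. At a residual rater ICC of 0.1 or below the variance loss is about 2% or less. The upper end needs an ICC of 0.3, which is more plausible if a new teacher rates at follow-up. The protocol does not say whether that happens, and gives neither the rater ICC nor the children per teacher, so no single value in the range can be preferred.

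**What to change.** Record a rater identifier on each Teacher SDQ, at baseline and at each follow-up. Add a random intercept for the teacher who rates at the follow-up being analysed, nested in school, to the primary mixed ANCOVA and to the models for other teacher-rated outcomes, alongside the planned school and intervention-group terms. State in advance that the teacher term is dropped only if its variance is estimated as zero or the model does not converge.

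The cost is one field on a form that researchers already collect in school and one extra random term. The identifier should be recorded at collection, since it may be hard to recover later. The downside is that with few children per teacher the variance may be poorly estimated, and the analysis may then revert to the model now planned.
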